### Framework for analysis

A common standardised protocol is being implemented across all study sites to ensure consistency in participant selection, interventions, and outcome assessments. The WHO coordinating team provides central training and oversight to harmonise activities, outcomes, and analytical procedures. All participating sites have extensive research experience, further supported by regular online and in-person meetings, data monitoring, and site visits by WHO monitors. The study started on 24 June 2021, and data collection was completed on 19 August 2024.

### Hypothesis/objective

For RCT1, the objective is to determine if outpatient care with injectable gentamicin (once daily) for two days and oral amoxicillin (twice daily) for seven days can be as cost- effective compared to the currently recommended management, that is, injectable ampicillin (2–4 times daily), and injectable gentamicin (once daily) with supportive care for seven days, for low-mortality-risk PSBI signs. This could significantly alleviate the burden on hospitals, and reduce the incidence of hospital-acquired infections while lowering costs for both health systems and households.

For RCT2, we compare the feasibility and CE of switching from continued inpatient care with seven days of recommended treatment using injectable ampicillin (2 − 4 times daily), and injectable gentamicin (once daily) with supportive care (control) to outpatient care (intervention) with oral amoxicillin (twice daily) for five days after a two-day hospital stay. YIs with moderate-mortality-risk PSBI are randomised into inpatient and outpatient arm after 2 days of inpatient treatment with injectable ampicillin (2 − 4 times daily), and injectable gentamicin (once daily) and a negative CRP test. If outcomes are shown to be non-inferior, and costs are lower with the intervention, then this approach would optimise the use of hospital resources and minimise household economic burden.

Collectively, the results from these trials will provide a strong foundation for revisiting and updating WHO PSBI management guidelines, ensuring that treatment strategies align with resource-constrained settings while maintaining clinical safety [24].

### Costs framework

The cost will be assessed from both the hospital and household perspectives. From the hospital perspective, medical treatment costs will be determined at each study hospital across all sites in both the intervention and control arms (**Table 1**, **Table 2**). Additionally, the household's costs will be separated into medical and non-medical costs. The hospital's indirect operational costs and households' opportunity costs in terms of wage loss will also be estimated. The costs will be weighted by infant days for each hospital, separately for the control and intervention arms, to obtain site-specific average costs for each item. To generate combined estimates, we will pool site-specific average costs across all sites to produce a single multi-country mean cost for inpatient and outpatient management, respectively.

**Table 1 T1:** Framework for provider costs under RCT1: outpatient versus inpatient management of young infants (0–59 days) with low-mortality-risk PSBI signs

Cost category	Intervention arm: outpatient treatment	Control arm: inpatient treatment
Place of treatment	Outpatient/ambulatory care	Hospital inpatient care
Antibiotic regimen	Injectable gentamicin once daily for 2 days plus oral amoxicillin twice daily for 7 days	Injectable ampicillin (2–4 times daily depending on age) plus injectable gentamicin once daily for 7 days
Staff costs	Outpatient assessment, counselling, injections preparation (canula), gentamicin administration, follow-up visits	Inpatient assessment, nursing care, injections preparation (canula) + administration, monitoring and supportive care
Medicine costs	Gentamicin and oral amoxicillin	Ampicillin and gentamicin
Consumables	Syringes, needles, cotton swabs, gloves, cannula, spirit	Syringes, needles, intravenous supplies, cotton swabs, gloves, cannula, spirit
Inpatient bed costs	Not applicable	Included for the duration of hospitalisation. Captures costs in the paediatric wards, such as costs of non- consumables, utilities, security, and laundry
Operational and indirect costs	Training, supervision, communication, administration and programme support	Training, supervision, communication, administration and programme support
Weighting approach for pooled analysis	Infant-days (number of infants treated and days each medicine or consumable is used)	Infant-days (number of infants treated and days each medicine or consumable is used)

PSBI – possible serious bacterial infection, RCT – randomised controlled trial

**Table 2 T2:** Framework for provider costs under RCT2: shorter versus standard hospital stay for young infants with moderate-mortality-risk PSBI signs

Cost category	Intervention arm: shorter hospital stays plus outpatient treatment	Control arm: standard inpatient treatment
Place of treatment	Initial hospitalisation for 2 days, followed by discharge home	Continued hospitalisation for 7 days
Antibiotic regimen	Injectable ampicillin plus gentamicin for 2 days, followed by oral amoxicillin twice daily for 5 days at home	Injectable ampicillin plus gentamicin for 7 days in the hospital
Eligibility for randomisation	Clinical improvement after 48 hours, negative CRP test and feasible follow-up	Not applicable
Staff costs	Initial inpatient assessment, injections preparation (canula) + administration, inpatient clinical monitoring, nursing and supportive care (for 2 days), discharge counselling, outpatient follow-up	Initial inpatient assessment, injections preparation (canula) + administration, inpatient clinical monitoring, nursing and supportive care (for 7 days), discharg
Medicine costs	Injectable antibiotics (gentamicin + ampicillin) for 2 days plus oral amoxicillin (twice daily) for 5 days	Injectable antibiotics (gentamicin+ ampicillin) for the full treatment duration
Consumables	Syringes, needles, CRP kits, cotton swabs	Syringes, needles, intravenous supplies, CRP kits, cotton swabs,
Inpatient bed costs	Indirect costs in paediatric wards, such as costs of non-consumables, utilities, security, laundry, *etc.* Included for the first 2 inpatient days	Indirect costs in the paediatric wards, such as costs of non-consumables, utilities, security, laundry, *etc.* Included for a full 7-day hospital stay
Operational and indirect costs	Training, supervision, communication, administration and programme support	Training, supervision, communication, administration and programme support
Weighting approach for pooled analysis	Infant-days (number of infants × days)	Infant-days (number of infants × days)

CRP – C-reactive protein, PSBI – possible serious bacterial infection, RCT – randomised controlled trial

The households incur out-of-pocket expenditures, which can be separated into direct medical expenses (registration/consultation, medicines, and consumables) plus other non-medical expenses (transport, food, and wage loss). For RCT2, laboratory costs for CRP tests are also included. Wage loss occurs due to loss of income due to absenteeism from work. Site-level costs per SYI will be based on the sample size under each item for both arms for each trial, but combined costs will depend on the number of enrolled infants at each site.

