Coverage of sick YIs (SYI) assessed, enrolled and treated under both RCT1 and RCT2 for control and intervention.Data on two outcome variables for all SYI covered under different treatment arms. Well-trained independent outcome assessor visits all enrolled cases on days two (only for RCT1), four, eight, and 15 after the initiation of treatment to assess the study outcomes in both intervention and control arms.Average annual salaries of nurses, paediatricians, medical officers and any other staff supporting treatment. To calculate staff costs per minute, data will be collected on the average number of days in a month and the average number of hours in a day that staff work.Staff time will be considered only for activities that are linked to hospital staff and not those linked to research staff, such as outcome assessment or treatment documentation (**Table 1**, **Table 2**). The activities for the staff time will be based on a pre-defined implementation strategy [21,22].Data will be collected for SYI that receive at least 80% of the treatment (recommended treatment) and those who receive <80% of seven-day (<5.5 days) treatment (partial treatment). The latter occurs due to a treatment failure, a change in treatment, readmission, left voluntarily, or death. For the recommended treatment, we will collect costs for the seven-day treatment period following the initial assessment, across both study arms and both trials. For partial treatment, medical costs will be calculated for an average treatment period of three days in RCT1 after the initial assessment, and for two days in RCT2 in both inpatient and outpatient arms after randomisation. Costs for enrolled SYI will be weighted by the proportion of participants receiving 80% recommended treatment and those receiving partial treatment, with weights set to SYI for each group. This prevents any child randomised and enrolled from being missed. Costs due to complications, changes in treatment, and/or readmission are outside the seven-day recommended treatment window in both study arms of both trials and will not be collected.Data on staff time per visit for an activity and the number of visits undertaken for each activity during the recommended treatment period will be collected by interviewing at least 3–5 staff of each type at each hospital.The staff time for all visits during the treatment period will be weighted by the number of days an infant receives the activity and the number of YI receiving the activity (defined as weighted by infant days). For the first activity assessment on presentation at the hospital, the number of SYI will be all enrolled for a given treatment, whether partial or recommended. For all other activities, SYI who receive 80% recommended treatment will be considered to have received seven days of treatment, and those receiving partial treatment for an average of three days to calculate the costs for those enrolled.The average exchange rate used to convert all the cost estimates in local currency into USD will be for 2024, the period for which the salaries of providers, prices and household costs will be reported. It will ensure consistency, and inflation rate adjustments will not be needed for cost calculations. The recommended treatment period will be seven days for inpatient treatment in the control arm and seven days for outpatient treatment in the intervention arm for RCT1. For RCT2, the average length of inpatient treatment is 48–72 hours, prior to a negative CRP laboratory test. In RCT2, the control group after randomisation will continue receiving inpatient care for five days, while the intervention group will be discharged from the hospital on oral amoxicillin for five days to be taken at home. Both arms will share the initial hospitalisation costs during the first two days in RCT2, including CRP test costs (including staff time, kits, and laboratory costs).The data on quantities used of injection gentamicin, injection ampicillin and oral amoxicillin will be as per the recommended treatment and partial treatment per SYI for each treatment arm under each RCT.The number of SYI receiving specific medicines and consumables for each arm under both RCTs will be calculated based on the numbers receiving recommended treatment and those receiving partial treatment.Information on types and quantities of consumables required with each medicine will be collected separately for each hospital and each arm under both RCTs. The cost of medicines and consumables will be charged per size in which they are dispensed. Medicine dosage varies with the weight of the YI [21,22]. Price will be taken for full strength, and the rest will be marked as wastage. Price data will be taken from the hospital's pharmaceutical department (if available); otherwise, the market price or the WHO price will be used.Data on annual financial expenditures and admissions in the newborn intensive care units or paediatric wards where YI with PSBI are treated as inpatients at the hospital will be collected and allocated based on patient days to calculate the inpatient bed costs/ SYI treated as an inpatient. These expenditures include administration, utilities, laundry, security, data management, internet, non-consumables and other costs in the hospital inpatient ward.Hospital ambulance to transport enrolled SYI under a specific treatment arm is a cost to the hospital. It is difficult to get this information separately for each enrolled SYI under different treatment arms from the hospital data. Indirect estimation based on the average trip cost and the number of SYI using free public ambulances, estimated from household data for each treatment arm in RCT1 and RCT2, will be used.Hospital data will also be collected for operational costs, which help to strengthen the assessment, identification, and treatment of SYI with PSBI. These include training, supplies, and communication. The total costs under these three will be estimated per SYI assessed. Staff training costs include the costs of development of training material and training cost per staff per day based on the per diems, honorarium for trainers, venue and refreshment costs. Total training costs will be calculated for all staff who were used to assess and treat SYI and will be estimated per SYI assessed. Training costs for research staff for outcome assessment or data collection will not be collected or included. Price and quantities of supplies used during the assessment, such as timers, thermometers and weighing scales, will be prorated for PSBI assessed. Communication costs, include job aids or educational material, and the cost of videos developed and played at the hospitals for educating the mothers about the danger signs. Data will be collected on item quantities and prices from hospitals to assess total costs and costs per SYI assessed.

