**Figure 1 F1:**
[figure not shown]
Pictorial representation of the steps for calculating staff costs per sick young infant for a given arm for a given trial. A – activities, F – hospital facilities, P – providers, TC – total costs, TSC – total staff costs, Tt – total time.

1 Average staff time per SYI will be calculated first at each hospital for a given staff type for each activity by multiplying the time (t = minutes per visit) and the number of visits/ SYI for the activity during the treatment period (V). The number of visits for an activity per SYI can range from one visit for assessment on admission to 21 visits for daily assessments, including vitals (generally three visits per day for 7 days of treatment). However, a given staff type, for example, one nurse may take a longer time or do more or fewer visits for an activity than another nurse at the same or another hospital. Hence, the total time (T) per SYI for each activity (A) per provider type (P) at a site under different arms and trials will be TPi = (average (ts × Vs)), where ‘i’ is for providers of the same type to get the time and visits information, and ‘s’ is for each staff member of a given provider type that is interviewed. Providers ‘i’ are nurses, medical officers/ general practitioners, paediatricians, or any other provider specified. We will take the average across providers of the same type to obtain the average time for an activity during the entire treatment episode for each arm in both RCTs.2 Staff time per provider ‘i’, per activity ‘j’ for a given hospital/facility (F) ‘k’ across all SYI getting recommended treatment will then be calculated as staff time per provider i per activity j for a given hospital k = T × N × %, where N is the number of SYI receiving activity for full days of recommended treatment (N), and % is the percentage of infants treated by a given provider for the given activity. Activity ‘j’ is described for RCT1 (**Table 1**) and RCT2 (**Table 2**) under control and interventions for staff time; ‘k’ is the hospital for which the data will be collected using the provider/hospital questionnaire.3 The average time will be aggregated for all activities for a given provider and facility by using the number of SYI receiving recommended treatment as weights for each activity.4 The total time for each staff will then be multiplied by the respective staff salaries/ minute (calculated based on annual salaries, the number of days worked in a year, and the number of hours worked in a day) at each hospital to obtain the staff costs/provider for treating all infants completing recommended treatment at a hospital.5 These staff costs will be added across the providers and then across the hospitals to obtain the total staff costs at a given site.6 These staff costs will be divided by the total number of SYI with recommended treatment under a given arm in each trial to get the staff costs/SYI for control and intervention separately for both RCTs (**Figure 1**).7 Likewise, staff costs per SYI will be calculated for each treatment arm under both RCTs for partial treatment.

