
### Estimation of medicines and consumables costs

The following steps will be followed to calculate the medicines and consumable costs per SYI at a given site:

For each medicine used under a given arm for a given trial, the total cost of a medicine for each SYI will be calculated by multiplying the price per vial or tablet for a medicine (P) by the quantities of medicines required per SYI (Q) for recommended treatment and the number of infants receiving the medicine (n). Average medicine quantities will differ by age and weight of the SYI [21,22], and there will be associated wastage when standard-sized injectables or tablets are used. For the hospitalised SYI, injection ampicillin is given twice daily in the first week of life, thrice daily in 2–4 weeks of life, and four times daily in four or more weeks of life. 500 mg vials will be used to draw the required doses based on the SYI’s weight and age. Assuming an average dose of 200 mg three times a day, at least two vials per day will be needed for a SYI, totalling 14 vials over seven days. With a daily requirement of 600 mg, the average wastage is 40%; at higher weights, it decreases to 25%. For gentamicin, an ampoule of 40 mg/ml or 20 mg/2 ml will be used, from which 8 mg, 16 mg, or 24 mg will be administered once daily, depending on the YI’s weight. Assuming an average requirement of 16 mg, seven ampoules of 20 mg will be needed for the control arm and two ampoules for the intervention arm in both RCT1 and RCT2. This would lead to an average wastage of 20%. For amoxicillin, 14 dispersible tablets of 250 mg will be required for seven days of treatment in RCT1 and 10 dispersible tablets for five days as an outpatient in RCT2. SYI <4 kg will require half a tablet, and those weighing >4 kg will require a full tablet. We assume, on average, 14 tablets will be dispensed for each SYI. Assuming half the SYIs are <4 kg and that, on average, only half a tablet is used from those dispensed, there would be 25% wastage.For each medicine at each hospital, the cost of each consumable will be calculated by multiplying the price per unit of the consumable (Pc) by the consumable quantities required per SYI (Qc) for recommended treatment with that medicine, and the number of infants receiving the consumable (n).The total cost of medicines will be estimated by adding the costs of all medicines at a given hospital that are needed for each arm for each RCT.Similarly, the total cost of the consumables will be estimated by adding the costs of all consumables corresponding to the medicines needed for each of the arms under the two trials at a given hospital.A few consumables are not linked to specific medicines but are related to the treatment of SYI, such as a cannula fixer, a cannula for intravenous injections, gloves, and CRP kits for protein laboratory test. These costs will also be calculated by multiplying the price per unit of the consumable (Pc) with consumable quantities required per SYI (Qc) for recommended treatment with that medicine, and the number of infants receiving the consumable (n) at the hospital.The total cost of consumables will be estimated by adding the costs of all consumables at a given hospital needed for each arm under the two trials.The total costs of medicines and consumables (estimated separately) at each site will be calculated by adding the costs at each hospital for each arm under the two trials.Average weighted medicine and consumables costs at a site will be calculated by summing the costs of all medicines and all consumables (separately) across all hospitals for each treatment arm. These total costs of medicines and consumables (estimated separately) will be divided by the number of SYI receiving recommended treatment at each hospital within a site to estimate medicine and consumable costs per SYI.For partial treatment, we will follow the same procedure (in steps 1–8) as for recommended treatment. Medicines and consumables will be calculated for three days for RCT1 and for two days after randomisation for RCT2. All medicines and consumables during the first two days of inpatient treatment will be common to both the recommended and partial treatment for RCT2.

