
### Estimation of hospital operational costs

Data collected for hospital indirect cost components – training, communications and supplies – are annual and relate to all infants assessed for PSBI during that year. For each site, expenses for training, communications and supplies will be added across facilities. The number of infants assessed during a year at a hospital will be estimated based on the total number of infants assessed over the entire study period and proportionally for 12 months. The sum of expenditures for each component will be weighted by the number of SYI assessed at each hospital for PSBI during the year to obtain the weighted expense per SYI at each site.Inpatient bed costs are shared costs across all infants and children admitted to newborn intensive care units and paediatric wards for shared items such as non-consumables, utilities, laundry, security, administration and other departmental expenses. The costs per admitted child will be estimated by dividing the total annual administrative expenditures (exclusive of staff costs, medicines, and consumables costs for enrolled SYI) of the paediatric and newborn intensive care units by the total number of children admitted in that year. These will be adjusted proportionately based on the average length of stay for enrolled SYI with PSBI relative to other SYI admitted during the year. We assume there are no inpatient bed costs for the intervention arm (outpatient) under RCT1 and for the 5-day ambulatory treatment in RCT2.Hospital transport/ambulance costs may be incurred for some patients brought to the hospital by public ambulance. Since it is difficult to obtain the data from the hospital database for each SYI enrolled, an indirect estimation method will be used. Household survey data will be used to determine the proportion of SYI who report using free public transport under different RCT treatment arms. Each site will calculate the average cost per trip based on the average distance to the hospital and the cost per km or mile. The cost per km depends on drivers' salaries, fuel costs for the average distance to hospitals in the study area, and vehicle maintenance costs at the site. Multiplying the average costs by the estimated number of SYI using public transport under each arm will provide an estimate of transport costs incurred at the hospital level.

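### RCT2 partial-treatment infants are costed for two post-randomisation days on medicines but for three undefined days on staff time, and the bed-cost rule is tied to neither

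*Protocol article*

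**What the plan says.** **Medical items.** The Hospital data section sets the partial-treatment length for medical costs at three days in RCT1 "and for two days in RCT2 in both inpatient and outpatient arms after randomisation". The section on medicines and consumables agrees: "Medicines and consumables will be calculated for three days for RCT1 and for two days after randomisation for RCT2".

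**Staff time.** Further on in Hospital data, the rule for staff activities after the first assessment counts "those receiving partial treatment for an average of three days to calculate the costs for those enrolled". It does not name a trial or say when the three days start. Step 7 under Estimation of staff costs makes clear that RCT2 is included: "staff costs per SYI will be calculated for each treatment arm under both RCTs for partial treatment".

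**Bed cost.** The article describes this in several places:
- Table 2, RCT2 control arm: "Included for a full 7-day hospital stay".
- Table 1, same row for the RCT1 control arm: "Included for the duration of hospitalisation".
- Estimation of hospital operational costs: "These will be adjusted proportionately based on the average length of stay for enrolled SYI with PSBI". Neither arm nor trial is named. The same section assumes no bed cost for the five ambulatory days of the RCT2 intervention arm.
- Hospital data: ward expenditure is allocated by patient days.
- Statistical analysis procedures: bed costs are among the items summed with infant-day weights for recommended and partial treatment.
- Site-wise and combined analysis plan: bed costs are weighted by the number of infants enrolled in the wards, with no split between recommended and partial treatment.

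**Cost window.** The CEA section limits the RCT2 ICER to costs after randomisation.

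**The concern.** One infant's episode should have one length, whichever cost item is being added up. Here the same RCT2 early stopper has two post-randomisation days of medicines and either one or three of staff time, depending on how an analyst reads the sentence. Two analysts working from this text could produce different RCT2 staff costs, and both would be following the plan.

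The bed rule matters for a different reason. After randomisation only the control arm carries bed cost, so an error in control bed days has no counterpart in the intervention arm and passes in full into the incremental cost, the ICER and the INB. The text leaves open which of several statements governs. It also leaves open whether the two-day rule for medical costs reaches beds at all. The abstract files bed cost under operational costs and the CEA section lists it apart from medical costs, but Statistical analysis procedures includes it in medical treatment costs.

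**Working it through.** The article gives no bed-day total and no partial-treatment rate, so there is no figure of its own to reproduce. The check compares the rules and counts days.

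**Inputs from the article**
- Full RCT2 course: 7 days, of which 2 precede randomisation (Table 2). Post-randomisation days: 7 − 2 = 5.
- Partial treatment, medical items: 2 days after randomisation, so 2 + 2 = 4 days from the start of treatment.
- Partial treatment, staff: 3 days, start not given.

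**Assumption.** The share q of an arm with partial treatment is taken as 2% to 20%.

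**Staff days per early stopper**
- Counted from randomisation: 3 against 2, which is +50%.
- Counted from the start of treatment: 3 − 2 = 1 against 2, which is −50%.

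The definition of partial treatment (below 5.5 days in total) does not settle the reading. The totals would be 2 + 3 = 5 or 2 + 1 = 3 days, and both fall under the cut-off.

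**Arm mean.** With two days for early stoppers, the mean number of post-randomisation days is 5(1 − q) + 2q = 5 − 3q. The three-day rule moves this by +q or −q. A literal seven-day bed charge for every control infant, of which 5 days fall after randomisation, would exceed it by 5 − (5 − 3q) = 3q.

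| q (assumed) | Mean days, 5 − 3q | Staff shift, ±q/(5 − 3q) | Bed excess if Table 2 is literal, 3q/(5 − 3q) |
|---|---|---|---|
| 2% | 4.94 | ±0.4% | 0.06 days, 1.2% |
| 5% | 4.85 | ±1.0% | 0.15 days, 3.1% |
| 10% | 4.70 | ±2.1% | 0.30 days, 6.4% |
| 20% | 4.40 | ±4.5% | 0.60 days, 13.6% |

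If bed cost is instead scaled to the control arm's own average stay, early departures already lower that average and the excess is zero at every q.

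**Effect on the difference between arms.** The staff rule names no arm, so it applies to both. The change in incremental staff cost is ±(q_I × w_I − q_C × w_C), where w is the staff cost of one partial-treatment day and I and C denote intervention and control. The two terms pull against each other. They cancel only if the products are equal, and Table 2 lists different staff activities by arm: inpatient monitoring and nursing in the control arm, counselling and outpatient follow-up in the intervention arm.

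**The case against.** A reader might infer from Table 2 that control infants who stop early are charged seven bed days, which would inflate the saving from early discharge. The documents do not support that. Table 2 is a framework for the planned regimen. Its control column also shows staff care for seven days and medicines for the whole course, yet the methods text plainly shortens medicines for partial treatment. It would be selective to let the bed cell alone override the methods text. The sections that describe bed costing point away from a flat charge: allocation by patient days, scaling to average stay, and inclusion in the sum weighted for partial treatment. This objection stands, and it removes any claim of a demonstrated bias in favour of the intervention.

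It can also be said that the three-day phrase is probably RCT1 wording carried over, since the trial-specific rule earlier in the same section is explicit. That is plausible, but the sentence as written has no such limit and step 7 of the staff costing covers both trials.

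Finally, the effect on arm means is small and partly offsets between arms. That also stands, and it limits the point to a correction of modest size.

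The bed ambiguity remains. The scaling sentence does not say whose average stay is used. An average taken over both RCT2 arms would pull the control stay down, whereas Table 2 read literally would push it up.

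**Conclusion.** The point holds as an inconsistency in the costing rules. For RCT2 partial treatment the article gives two days after randomisation for medical costs, medicines and consumables, and three days of unspecified start for staff activities. The difference is +50% or −50% of staff days per early stopper. On an assumed 2% to 20% stopping early, it is about ±0.4% to ±4.5% of an arm's mean staff days, with partial offset in the incremental cost. Its net direction cannot be known from the article.

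The bed rule is unreconciled, but no passage states an over-charge. The excess of 3.1%, 6.4% or 13.6% (assumed 5%, 10% or 20% stopping early) is an upper case that arises only if Table 2's fixed stay is applied to every control infant. It is zero if the control arm's own average stay is used. Both matters feed the RCT2 ICER and INB and should be corrected in the text.

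**What to change.** 1. In Hospital data, limit the three-day staff sentence to RCT1. State that RCT2 staff time for partial treatment uses the plan's own two post-randomisation days, as medicines and consumables do.
2. In Table 2, replace the fixed seven-day wording in the control bed cell with the Table 1 wording, which follows the length of the hospital stay.
3. In Estimation of hospital operational costs and in the Site-wise and combined analysis plan, state that the RCT2 bed cost entering the ICER uses the average post-randomisation stay of that trial's control arm, with partial-treatment infants included.

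These are costing rules only and touch no clinical instruction. Costing every item from each infant's recorded days is not needed, because the aggregate approach works once the durations agree. The cost is a text correction and a recalculation in the Excel workbook. The stated saving may become slightly smaller if the workbook now uses the fixed stay.
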